## Abstract

**Background:**

Prenatal diagnostics is a crucial process for ensuring the health of both pregnant women and their fetuses. However, the participation rate of high-risk pregnant women in prenatal diagnostics is often influenced by various factors, including anxiety, depression, and lack of family support. In recent years, mobile health (mHealth) interventions have become an important tool in improving maternal health management, especially in terms of behavior change. The Behavior Change Wheel (BCW) theory and the Family Health Theory (FHT) have been applied in various health interventions, but there are limited studies focusing on prenatal diagnostics.

**Objective:**

The study aims to evaluate the impact of a mobile health intervention based on the Behavior Change Wheel theory and Family Health Theory on prenatal diagnostic participation rates and pregnancy outcomes in high-risk pregnant women, while exploring the role of family member involvement in improving maternal psychological health and pregnancy outcomes.

**Methods:**

The study outlines a single-blind, interventional, randomized controlled trial conducted at the Inner Mongolia Maternity and Child Health Care Hospital. A total of 58 high-risk pregnant women will be included and randomly assigned to either the intervention group (29 participants) or the standard care group (29 participants). The intervention group will receive a 12-week mHealth intervention via the WeChat platform, including health education, emotional support, behavioral feedback, and family member participation. The standard care group will receive standard prenatal care. Primary outcomes include prenatal diagnostic needs and pregnancy outcomes, while secondary outcomes include health knowledge, anxiety and depression levels, decision conflict, and other factors. This study uses IBM SPSS Statistics 24.0 for data analysis, employing descriptive statistics, normality tests, Mann–Whitney U, Wilcoxon, and chi-square tests.

**Discussion:**

The study proposes that a mobile health intervention based on the Behavior Change Wheel theory and Family Health Theory may effectively increase prenatal diagnostic participation and improve the psychological health and pregnancy outcomes of high-risk pregnant women. The active participation and emotional support of family members are expected to be key components in achieving these improvements. This research provides new insights and evidence for the application of mHealth interventions in prenatal screening.

## Introduction

1

Birth defects refer to abnormalities in the structure, function, or metabolism of a baby that result from genetic, environmental, or their interaction, occurring before birth (1). As one of the leading causes of disability and death in children, birth defects have profound physical and psychological effects on the affected children and their families, while also imposing a significant socio-economic burden (2–4). According to the latest epidemiological data, the incidence of birth defects in China is approximately 6%, with around 900,000 new cases reported annually, and this rate continues to rise (5, 6). A meta-analysis study by Blencowe et al. reported that the global birth defect rate in live births is approximately 2%-3%, equating to about 8 million new cases of birth defects each year, based on data from high-income, middle-income, and low-income countries (7). This highlights the global public health significance of birth defects, as well as significant regional differences in incidence, influenced by social, environmental, and biological factors. It is worth noting that for many severe congenital abnormalities, existing treatments are mostly palliative, and curing these defects is difficult (8, 9). Therefore, strengthening preventive interventions for birth defects has crucial public health implications.

The prevention strategies for birth defects are typically divided into three levels: primary prevention, secondary prevention, and tertiary prevention (10). Primary prevention focuses on reducing the risk of birth defects through preconception interventions, including health education, appropriate nutritional supplementation, preconception care, and genetic counseling (11). Secondary prevention is mainly carried out during pregnancy, involving prenatal screening and diagnosis techniques to identify high-risk fetuses early and implement interventions to reduce the incidence of birth defects (12). Tertiary prevention occurs in the neonatal period, focusing on early screening and timely treatment to minimize the clinical consequences of birth defects and improve the quality of life of affected children (13). In secondary prevention, prenatal screening plays a key role, aiming to identify high-risk fetuses early and providing a basis for subsequent prenatal diagnosis. Current major techniques for prenatal screening include imaging examinations (such as ultrasound), serological screening (e.g., Down syndrome screening), and molecular biology methods (e.g., non-invasive prenatal testing, NIPT), with a combined detection rate of up to 98.2% (14).

Despite significant progress in prenatal screening technologies, the diagnostic rate of prenatal screening in China remains relatively low, particularly among high-risk pregnant women (15). Notably, even when high-risk pregnant women receive enhanced prenatal care, this gap persists, as they often face barriers to completing confirmatory diagnostic procedures (e.g., amniocentesis). For instance, some women decline invasive diagnostic testing due to fears of miscarriage, financial constraints, or inadequate counseling. The popularity of prenatal diagnosis and its acceptance by pregnant women are influenced by various factors, including health literacy, the importance they place on prenatal screening, misconceptions about diagnostic risks, and concerns or fears about potential risks (16–18). Therefore, improving prenatal diagnosis rates among high-risk pregnant women through effective interventions that address these specific barriers is an urgent public health issue, as this population carries a substantially elevated baseline risk of fetal anomalies.

With the rapid development of mobile health technology (mHealth), digital health tools such as smartphone applications and WeChat platforms have gradually become important carriers of health interventions (19, 20). Studies have shown that mHealth technology has significant effects on improving maternal and child health. Ameyaw et al. confirmed through empirical research that mobile health applications effectively improve maternal nutrition and significantly reduce the risk of pregnancy complications (21). Atukunda and other scholars further discovered that providing personalized health information through SMS and audio messages and involving pregnant women’s social support networks (including family and friends) can significantly increase the utilization of maternal health services (22). In China, WeChat, with its convenience and wide user base, has become an important tool for maternal health management. This platform not only provides personalized health guidance to pregnant women but also promotes the acquisition and practical application of health knowledge through interactive online consultations and health education push notifications (23). WeChat is a multi-functional social platform developed by Tencent, with over 1 billion active users worldwide. It supports text, voice, and video messaging between individuals and allows users to create group chats with up to 500 members for large-scale interactions. Additionally, the “Moments” feature enables users to share updates, photos, and videos, similar to social media feeds. WeChat also supports Mini-Programs, which allow third-party developers to offer various services, including health consultations and online medical services. Based on this evidence, the present study believes that mobile health interventions, especially those using WeChat platforms, are highly suitable for increasing prenatal diagnosis rates among high-risk pregnant women, thereby improving their pregnancy outcomes. Although existing public health studies have confirmed that various interventions can increase the prenatal diagnosis rate among high-risk pregnant women, there is currently a lack of systematic research guided by health behavior theory models focusing on prenatal diagnosis rates (24). Therefore, this study aims to use the WeChat platform as a mobile health intervention tool guided by the Behavior Change Wheel theory and Family Health Theory, to improve adherence to prenatal diagnostic procedures among high-risk pregnant women, and enhancing their pregnancy outcomes.

The Behavior Change Wheel (BCW), shown in **Figure 1**, was developed by Susan Michie and her research team in 2011 as a systematic framework for behavior change interventions (25). The theory integrates 19 related behavior change models and aims to help intervention designers understand why individuals fail to engage in specific behaviors, establish behavior goals, and select the core focus of interventions, providing a clear implementation path for systematic behavior change. Meanwhile, Sharon Denham innovatively introduced the concept of “family health,” which breaks the traditional focus on individual health in research (26). Based on this, Weiss-Laxer and other scholars further developed a more comprehensive conceptual framework for “family health” using the Delphi Method, as shown in **Figure 2** (27). They define “family health” as a comprehensive resource dependent on the family unit, derived from the health status, abilities, behavioral traits, personality, and internal interactions of family members, as well as the synergistic effects of external resources like physiological, social, emotional, economic, and medical support that the family can access. Therefore, combining the BCW and Family Health Theory provides a new theoretical perspective and practical approach for health behavior interventions, especially within the context of the family as a basic social unit. By integrating environmental factors from the BCW theory, the COM-B model (Capability, Opportunity, Motivation), and intervention functions, along with key elements from Family Health Theory, such as internal family interactions, family resource acquisition, and external family support, this approach offers a scientifically grounded and effective intervention plan for improving the overall health behaviors of individuals and families. Based on this, the current study will use the BCW and Family Health Theory as the theoretical foundation to develop a health education intervention model targeting high-risk pregnant women, aiming to improve their rate of prenatal screening and enhance pregnancy outcomes.

**Figure 1 f1:**
[figure not shown]
Behavior change wheel theory.

**Figure 2 f2:**
[figure not shown]
Conceptual framework of family health.

## Methods

2

### Design

2.1

This study is a single-blind, interventional randomized controlled trial conducted at the Inner Mongolia Maternity and Child Health Care Hospital. The aim is to evaluate the impact of a mobile health intervention based on the Behavior Change Wheel theory and Family Health Theory on the prenatal diagnosis rate and pregnancy outcomes of high-risk pregnant women undergoing prenatal screening. The study will be conducted from June 2025 to June 2026. The flowchart of the study is shown in **Figure 3** and **4**.

**Figure 3 f3:**
[figure not shown]
Flow chart of participants recruitment and study implement.

**Figure 4 f4:**
[figure not shown]
Timeline for study enrollment, intervention, and evaluation study setting and randomization.

### Participants

2.2

The participants in this study will be high-risk pregnant women undergoing prenatal screening at the Inner Mongolia Maternity and Child Health Care Hospital. Prior to enrollment, the research team will assess eligibility and have participants sign informed consent before randomly assigning them to either the intervention or standard care group, with 29 participants in each group, totaling 58 participants. The inclusion and exclusion criteria are as follows:

**Inclusion Criteria**

Aged 18 years or older.High-risk pregnancy as determined by prenatal screening results.Basic ability to use mobile devices and WeChat.Willingness to participate and sign an informed consent form.

**Exclusion Criteria**

No fixed contact information, no family member available for contact, or unable to be reached via phone or WeChat.Use of any psychiatric medications.Presence of mental symptoms such as unclear consciousness, speech difficulties, or lack of cooperation.Presence of severe systemic diseases or serious physical dysfunction.Participation in other clinical trials.Any other reasons deemed unsuitable for participation.Women who have been diagnosed with genetic diseases or have already undergone prenatal diagnosis.

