### Sample size estimation

2.3

This study is a randomized controlled trial, where the intervention group will receive the mobile health intervention and the standard care group will receive standard care. The outcome measure is the prenatal diagnosis demand. Based on previous randomized controlled trials related to willingness to undergo screening for related diseases, the intervention group’s demand proportion is 53.4%, and the standard care group’s is 34%, showing an increase of approximately 19.4% (28). We predict that the mobile health intervention based on the Behavior Change Wheel theory and Family Health Theory may lead to a doubling of the demand proportion (38.8%), reaching 72.8% (29). The expected demand proportion for the intervention group is 72.8%, and for the standard care group is 34%. Using a two-sided test with α = 0.05, β = 0.2, and power (1-β) = 80%, the sample size ratio between the two groups is 1:1. After using the PASS software (version 2021) to calculate the relevant values, it was determined that 23 participants per group would be required. Considering a 20% dropout rate, the final sample size for each group is 29 participants, for a total of 58 participants.

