### Intervention

2.6

This study established a multidisciplinary team consisting of genetic experts, nursing specialists, genetic doctors, and public health experts. Through several rounds of in-depth discussions, team members combined their expertise to develop comprehensive intervention strategies aimed at addressing the behavioral barriers to prenatal diagnosis participation among high-risk pregnant women, incorporating mobile health technology as a key tool.

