#### Primary outcomes

2.8.1

The primary endpoints are the demand for prenatal diagnosis and pregnancy outcomes. Demand is defined as the perceived or expressed need, typically associated with changes in health status. Demand is measured at the individual level both before and after the intervention. A participant is considered to have a screening demand if they answer “yes” to at least one of the following three questions: willingness for diagnosis, plans for prenatal diagnosis within six months, or having undergone diagnosis. The overall demand is the union of these three items. For participants who report having been diagnosed, the researchers will verify the diagnosis by reviewing relevant documents or appointment cards.

Pregnancy outcomes include full-term birth, preterm birth, miscarriage, induced labor due to social factors, and induced labor due to chromosomal abnormalities.

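### Entry screens out only one of the three answers that make the demand endpoint positive, so women already willing or planning dilute it; Month 0 demand should be a stratifier

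*Protocol article*

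**What the plan says.** Section 2.8.1 makes demand for prenatal diagnosis one of two primary endpoints. The rule is: "A participant is considered to have a screening demand if they answer “yes” to at least one of the following three questions". In short, the items ask whether she is willing, whether she has a plan for the next six months, and whether the diagnosis has already been done. Section 2.8.1 then combines them: "The overall demand is the union of these three items". On timing: "Demand is measured at the individual level both before and after the intervention". Table 1 places the measurements at Month 0, Month 3 and after delivery.

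The inclusion criterion on risk reads "High-risk pregnancy as determined by prenatal screening results". The only criterion touching any demand item is the last exclusion: "Women who have been diagnosed with genetic diseases or have already undergone prenatal diagnosis". No criterion in section 2.2 concerns willingness or plans.

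Section 2.3 sizes the trial on demand alone, comparing 72.8% with 34%. The rates are introduced as "Based on previous randomized controlled trials related to willingness to undergo screening for related diseases". The section does not say whether they describe all entrants or only women without demand at entry.

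Section 2.4 describes one unstratified Excel list with numbered envelopes. Section 2.9 mentions no use of Month 0 demand.

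**The concern.** Entry and endpoint do not match. Removing women who have already had the diagnosis fits the idea that someone already at the target should not be enrolled to be moved there. But the endpoint counts three answers as the target, and eligibility acts on one.

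A woman who is willing or planning at Month 0 is positive before the programme starts. If she goes on to have the diagnosis, the union records no change. The only change it can record for her is a loss of demand.

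Such women are plausible here. Entrants already have a high-risk screening result, so diagnosis is the next decision they face. The planning rates come from willingness to be screened, which is a different decision.

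The more women enter positive, the smaller the between-arm difference that a given programme effect can produce. With 58 women there is little room for that. An SAP could specify an adjusted analysis, and its absence from an article is not the point. But eligibility, the randomisation list and the meaning of the planning rates are fixed in this document.

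**Working it through.** **Inputs.** From section 2.3: 34% and 72.8%, two-sided 0.05, 80% power, 1:1 allocation, 23 evaluable and 29 enrolled per arm. The share positive at Month 0, *b*, is not given, so it is varied as an assumption.

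**1. The plan's own figure.** The unpooled formula gives
n = (1.960 + 0.842)² × (0.728×0.272 + 0.34×0.66) / 0.388² = 22.02, rounded up to 23.
Then 23/0.80 = 28.75, rounded up to 29. The arithmetic reproduces. At 23 per arm, exact power of the uncorrected chi-square test is 78%.

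**2. Conversion implied by the plan.** Going from 34% to 72.8% means that 38.8/66 = 58.8% of women who would otherwise say no are converted.

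**3. Hold that conversion and vary the control rate c.** The intervention rate is c + 0.588(1 − c). The stratified column uses an uncorrected Cochran-Mantel-Haenszel test by Month 0 demand (simulated). It assumes that entry-positive women stay positive and that a fraction s = 5–20% of women without demand convert spontaneously.

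| Control rate | Intervention rate | Difference (points) | Unadjusted power | Stratified power |
|---|---|---|---|---|
| 34% (plan) | 72.8% | 38.8 | 78% | 86–96% |
| 50% (assumed) | 79.4% | 29.4 | 56% | 74–89% |
| 60% (assumed) | 83.5% | 23.5 | 43% | 64–80% |
| 70% (assumed) | 87.6% | 17.6 | 32% | 51–64% |

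In this model the share positive at entry is b = (c − s)/(1 − s). At c = 34% that is 0.29/0.95 = 30.5% for s = 5% and 0.14/0.80 = 17.5% for s = 20%. At c = 50% it is 0.45/0.95 = 47.4% and 0.30/0.80 = 37.5%. Entry-positive women contribute nothing to the stratified test, so the comparison rests on women who can convert. Their rates are 5% against 0.05 + 0.588×0.95 = 60.8% (using the unrounded conversion), or 20% against 0.20 + 0.588×0.80 = 67.0%.

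**4. The other reading of 34% and 72.8%.** If these are rates among women without demand at entry, each observed rate becomes b + (1 − b)p and the difference shrinks to 38.8 × (1 − b) points. By the pooled approximation, for 23 per arm:
- b = 0: 38.8 points, power 77%
- b = 20%: 31.0 points, 59%
- b = 50%: 19.4 points, 34%

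If the rates already describe all entrants, the sample size is unchanged. But if 34% were also the share positive at entry, the plan would need 58.8% conversion under the programme and none under standard care.

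**The case against.** Four arguments count against a stronger version of this point.

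**Entry-positive women are not beyond the programme's reach.** A reader might infer that they have no barrier left and cannot respond. The protocol does not support that. The Introduction describes barriers to completing diagnosis (fear of miscarriage, cost, poor counselling). The Enablement strategies and Phase 2 in section 2.6.1 include reminders and counselling for families with an appointment. The stated purpose is "addressing the behavioral barriers to prenatal diagnosis participation among high-risk pregnant women". Keeping a woman from losing demand would also register on the endpoint. What stands is narrower: she cannot move from no to yes.

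**The size of the loss is assumed.** No passage gives control rates of 50–70%, and the 34% may already include women willing at entry. A reader might infer that the trial is underpowered, or that the planned gain is impossible. The 38.8-point gain is impossible only above a 61.2% control rate (100 − 38.8), and nothing in the article says demand is that high.

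**Changing eligibility is not the only remedy.** The table shows that using Month 0 demand recovers much of the loss. The gain shrinks with a continuity correction, which removes it at 70%. It also depends on the assumption that entry-positive women keep their demand.

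**All-comer enrolment is legitimate.** The stated aim concerns high-risk pregnant women generally and includes pregnancy outcomes as the other primary endpoint. Excluding willing women would narrow that question. Nor is there systematic bias, because randomisation balances such women on average, although chance imbalance is possible with 58.

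**Conclusion.** The mismatch is in the text: three answers define the endpoint, and entry screens out one. Women willing or planning at Month 0 are eligible, already positive, and able only to keep or lose demand. The consequence is dilution and lost power, conditional on a share that the article does not state; it is not bias.

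At the plan's own 34% control rate, unadjusted power is 78%, close to target. At an assumed 50% it is 56%. Using Month 0 demand brings these to about 86–96% and 74–89%. All of these figures assume 58.8% conversion and 23 evaluable women per arm; the stratified ones also assume 5–20% spontaneous conversion, no loss of demand among entry-positive women, and no continuity correction.

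The documents do not support the conclusion that willing women must be excluded.

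**What to change.** - Ask the three demand items before the envelope is opened and say so in section 2.4. Month 0 in Table 1 does not settle the order, and answers given after allocation could not serve as a baseline.
- Stratify randomisation by Month 0 demand (yes/no), with a separate list and envelope series for each stratum. Stratum sizes are not known in advance, so use blocks within each list to keep the arms balanced.
- Analyse the demand endpoint stratified by, or adjusted for, Month 0 demand, for example with Cochran-Mantel-Haenszel or logistic regression. Report new demand among women who had none at Month 0.
- State in section 2.3 whether 34% and 72.8% refer to all entrants or to women without demand at entry, and check the sample size against that choice.

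The cost is a second randomisation list and slightly more analysis; Month 0 demand is already collected.

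Restricting entry to women who answer no to all three items is an optional design choice. It would shrink the eligible pool and limit the conclusion to women without demand at entry, so it should be weighed against the stated aim.
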